## Methods and trial design

### Study design and setting

The CURE RCT is a two-arm RCT comparing model-based mechanical ventilation (MBV) with current standard practice mechanical ventilation (SPV) in patients with a ratio of partial pressure of arterial blood oxygen (PaO2)/fraction of inspired oxygen (FiO2) (P/F ratio) ≤ 200. It is to be conducted in a single-centre hospital intensive care unit (ICU) at Christchurch Hospital in Christchurch, New Zealand.

The primary objective is to assess the impact of model-based ventilation in PEEP selection (MBV) therapy on clinically significant patient outcomes and patient-centred quality of care metrics. The other objectives of this study include (1) to provide the knowledge and methods to make care more patient-specific and timely to optimise treatment and improve outcomes in a large cohort of critically ill patients and (2) to improve the understanding of the pathophysiological basis of critical illness through what we learn about the hourly and daily evolution of lung injury in terms of patient-specific elastance and response to care through this study.

The primary outcome of this study is the area under the curve (AUC) of PaO2/FiO2 over the period of mechanical ventilation. Secondary outcomes include length of time of MV (LoMV), ventilator-free days (VFD) up to 28 days, ICU and hospital length of stay (LoS), AUC of SpO_2_ (oxygen saturation)/FiO_2_ during MV, number of desaturation events (frequency and fraction of time SpO_2_ < 88%), changes in respiratory mechanics and chest x-ray index scores, rescue therapies (prone positioning, nitric oxide use, extracorporeal membrane oxygenation (ECMO)) and hospital and 90-day mortality. These outcomes and their corresponding four levels of specification based on Zarin et al., 2011 is shown in Table 1. The secondary analysis includes comparison of the means of LoMV, VFD, hospital and ICU LoS, 90-day mortality, chest x-ray index scores and rescue therapies used.

**Table 1 Tab1:** Four levels of specification in primary and secondary outcomes

Level 1 Domain	Oxygenation		MV		Length of stay			Other	
Level 2 Specific domain	AUC P/F ratio	AUC Spo2/FiO2	Length of MV	Ventilator free days (VFD) up to 28 days	Hospital	ICU	90-Day mortality	Chest x-ray index scores	Rescue therapies
Level 3 Specific metric	Difference in AUC		Number of days	28 days – days of MV	Number of days		Time to event	Index scores over period of MV	Number of therapies used

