Level 4 Method of aggregation	Comparisons of the of means of AUC		Comparisons of the means of number of days	Comparisons of the means of VFD	Comparisons of the means of length of stay		Comparison on number of 90-day mortality	Comparison of index scores over time	Comparison of rescue therapies used.

*P/F* partial pressure of arterial oxygen/fraction of inspired oxygen, *SPO*_*2*_ oxygen saturation, *MV* mechanical ventilation, *FiO*_*2*_ fraction of inspired oxygen

A difference in primary and secondary outcomes will show the impact of MBV compared to SPV. No difference would show that enhanced, model-based metrics of patient-specific condition have no effect on patient-centred or clinical outcomes. Either outcome will yield clinical guidance.

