### Study outcome

The trial will utilise a primary composite end point incorporating the AUC of the P/F ratio over the period of MV. Every participant in the intervention (MBV) group is compared with every participant in the control (SPV) group. Test statistics will be calculated using the one-sided Wilcoxon rank sum test at alpha of 0.05. If results show no statistically significant difference between the intervention and control, it will result in the rejection of the intervention treatment as a standard of care and thus, the secondary clinical outcome assessments will include the number of desaturation events measured as peripheral capillary oxygen saturation < 90%, LoMV, VFD for 28 days, the quality of mechanical ventilation care measured as the AUC of SpO_2_/FiO_2_ and chest x-ray index scores over time. The test statistic will be calculated using the one-sided Wilcoxon rank sum test at alpha of 0.05.

A difference in the primary outcome will show the impact of MBV compared to SPV. No difference would show that enhanced, model-based metrics of the patient-specific condition have no effect on patient-centred or clinical outcomes. Either outcome will yield clinical guidance.

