### Sample size study

A Monte-Carlo simulation was performed to determine the sample size and determined that a minimum effective sample size of approximately 160 patients per arm is required to identify a 25% reduction in median LoMV, with 0.8 power, at a double-sided significance level of 5% [37].

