### Stopping rule

A linear alpha spending approach will be used for early termination of the trial for safety. Linear alpha spending falls between a Pocok and O’Brien-Fleming boundary [38]. With analysis points of 50, 75, 100, 125 and 160 patients per arm, and assumed control group mortality of 0.2, the mortality difference required to stop the trial (Mortality_Intervention_ – Mortality_control_) at each analysis point respectively is 0.20, 0.16, 0.14, 0.12 and 0.10. This approach has cumulative α = 0.025.

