### Adverse event (AE) and SAE reporting

(AEs are defined as any unexpected change in physiology in a study participant associated with either the RM_max_ or PUMP. This does not necessarily have to have a causal relationship with the aforementioned procedures. Typically, this would be an unexpected, non-life-threatening event, which rapidly resolves following simple corrective measures. For example, hypotension will occur in most participants undergoing an RMmax or PUMP. However, if the procedure had to be shortened or abandoned, but the participant recovered with simple corrective measures (e.g. temporarily increasing noradrenaline by ≥ 5 mcg/min) or giving > 500 ml fluid bolus) this would be recorded as an AE. It is very important these events are accurately recorded as risk factors for AEs that need to be defined when carrying out RMs (as seen in Additional file 3).

SAEs are defined as any untoward medical occurrence that (1) results in death; (2) is life-threatening; (3) prolongs hospitalisation or (4) results in disability or incapability. However, baseline mortality in the patients in intensive care who are enrolled in the trial will likely be high due to the critical illness necessitating admission to the ICU. Despite attempts at prevention, trial participants will frequently develop life-threatening organ failure(s) unrelated to study interventions. Events that are a part of the natural history of the primary disease process or expected complications of critical illness will not be reported as SAEs in this trial. Additionally, events already defined and reported as study outcomes, such as mortality or re-admission to the ICU, will not be labelled and reported separately as SAEs unless they are considered to be causally related to the study intervention or are otherwise of concern in the investigator’s judgement.

SAEs will be reported to the principal investigator within 24 h of any investigator becoming aware of the event. The minimum information to report includes:
Patient trial identifierThe nature of the eventThe time the event commenced and ceasedAn investigator’s opinion of the relationship between study involvement and the event (not related, unlikely, possibly, probably or definitely related)Whether treatment was required for the event and what treatment was administered

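### Table 1 defines ventilator-free days as 28 minus days of MV with no term for death, so days after an early death count as ventilator-free

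*Protocol article*

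**What the plan says.** Under Study design and setting, the protocol article lists "ventilator-free days (VFD) up to 28 days" among the secondary outcomes. Table 1 in the same section specifies each outcome at four levels. For VFD the metric is "28 days – days of MV" and the aggregation is "Comparisons of the means of VFD". The Study outcome section names "LoMV, VFD for 28 days" among the secondary assessments and adds "The test statistic will be calculated using the one-sided Wilcoxon rank sum test at alpha of 0.05".

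VFD is also mentioned in the abstract, the list of collected patient information and the abbreviations. None of these gives a score for a patient who dies before day 28, whether on or off the ventilator. Hospital and 90-day mortality are separate outcomes and are not linked to VFD.

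Deaths are expected. The Stopping rule section uses an "assumed control group mortality of 0.2", and the section on adverse events says that "baseline mortality in the patients in intensive care who are enrolled in the trial will likely be high".

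**The concern.** VFD is meant to be high when a patient does well. The formula in Table 1 subtracts only time on the ventilator and ignores vital status. A patient who dies early has few ventilator days and so scores near the top of the scale, above survivors who needed a week or more of support.

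With about 20% of patients dying (0.20 × 160 = 32 in the control arm), this affects a sizeable part of the sample. If the intervention changed mortality, VFD could move in the wrong direction or fail to show harm. Because the test is one-sided, an upward shift caused by deaths could be declared a benefit.

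**Working it through.** **Inputs from the protocol article.** VFD formula and comparison of means (Table 1); one-sided Wilcoxon rank sum test at 0.05 (Study outcome); control mortality 0.20 (Stopping rule); 160 per arm (Sample size study).

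**Assumed inputs (not in the documents).** MBV mortality of 30%; the same liberation times in both arms, log-normal with median 7 days and log-SD 0.9; log-normal death times with log-SD 0.7 and median varied from day 2 to day 10; deaths occur on the ventilator; no early stopping.

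**The plan's own figure.** The article gives no VFD figure to reproduce. Its sample size statement is "160 patients per arm is required to identify a 25% reduction in median LoMV, with 0.8 power, at a double-sided significance level of 5"%, without the LoMV distribution, so 160 cannot be checked exactly. On a log-normal scale, n per arm = 2(1.96 + 0.84)²σ²/(ln 0.75)². At σ = 0.9 this gives 154, and 160 corresponds to σ of about 0.92. The assumed log-SD of 0.9 is therefore in line with the plan's own size. The VFD point does not depend on it.

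**Step 1: single patients, formula as written.**
- Death on MV day 2: 28 - 2 = 26. Day 3: 25. Day 7: 21.
- Survivor ventilated 7 days: 21. Ten days: 28 - 10 = 18. Fourteen days: 14.

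**Step 2: difference in mean VFD.** Let all deaths occur on day d and all survivors be ventilated for L days, with mortality m₁ (MBV) and m₀ (SPV).
- As written: (m₁ - m₀) × (L - d).
- With death = 0: -(m₁ - m₀) × (28 - L).

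Take m₁ - m₀ = 0.10 and L = 10. For d = 2 the difference as written is 0.10 × 8 = +0.8 days, and for d = 7 it is +0.3 days. With death = 0 it is -0.10 × 18 = -1.8 days in both cases. The sign as written turns on whether deaths come before or after the typical survivor's liberation.

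**Step 3: simulation under the assumed inputs** (4,000 trials per row, 160 per arm, 30% v 20% mortality):

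| Median death day | Mean difference, as written | Benefit declared, as written | Mean difference, death = 0 | Benefit declared, death = 0 |
|---|---|---|---|---|
| 2 | +0.7 d | 31% | about -1.9 d | about 0% |
| 4 | +0.4 d | about 15% | about -1.9 d | about 0% |
| 7 | +0.1 d | 5% | about -1.9 d | about 0% |
| 10 | -0.2 d | 2% | about -1.9 d | about 0% |

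With equal mortality (20% v 20%) the formula as written declares benefit in about 5% of trials at every death time, which is the nominal level.

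**Step 4: the mortality stopping rule.** The article's boundaries are differences of 0.20, 0.16, 0.14, 0.12 and 0.10 at 50, 75, 100, 125 and 160 per arm. With deaths assumed known at each look, a true 30% v 20% contrast crosses a boundary by 125 per arm in about 45% of trials and by 160 per arm in about 58%. The table above ignores this rule.

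**The case against.** The best defence has four parts.

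1. **Death timing drives the result, and the documents do not give it.** This stands. A reader might infer that the formula always rewards lethality. It does not: with deaths on the ventilator around day 10, the difference as written is slightly negative. The eligibility criteria also exclude patients not expected to survive 72 hours or 90 days. That is a prediction and cannot prevent early deaths, but it argues against assuming that they dominate. What remains for later deaths is masking: about -0.2 days as written, where scoring death as 0 shows about -1.9.

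2. **The distortion needs a real mortality difference, which would be seen elsewhere.** This also stands. Mortality is reported in its own right, and the stopping rule would end some of these trials early. Neither corrects the VFD result in a trial that runs to completion.

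3. **A table cell in an article is shorthand, and a fuller analysis plan may add a death rule.** That is possible. But the cell states an explicit formula rather than leaving the matter open, so such a rule would have to override Table 1.

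4. **LoMV and length of stay have the same problem.** A reader might extend the point to these outcomes and, through LoMV, to the sample size. The documents do not support that. Table 1 gives only a number of days for them, which is a unit and not a scoring rule. Handling of deaths there is commonly left to the analysis plan, and reasonable statisticians differ on the method.

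**Conclusion.** The VFD definition in Table 1 is wrong as written: it counts days after death as ventilator-free. That conclusion follows from the formula alone and needs no assumptions.

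The size does rest on assumptions. For a 10-point mortality excess under MBV, the mean VFD difference runs from about +0.7 days (median death on day 2) to -0.2 days (day 10), against about -1.9 days with death scored 0. False benefit ranges from about 31% down to 2% of trials. Only the 20% control mortality and the arm size come from the article. The MBV mortality, death times and liberation times are illustrative, and early stopping is left out.

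A reader might infer that the trial's main conclusion is at risk. It is not. VFD is one of many unranked secondary outcomes, the primary outcome (AUC of P/F) is unaffected, and the error rate is not inflated when mortality is equal. This is a should-fix point.

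**What to change.** Change the VFD metric in Table 1 to: VFD = 0 if the patient dies by day 28; otherwise 28 minus the days of invasive MV up to day 28 (minimum 0), counting days of re-ventilation after extubation. Use the same definition wherever VFD is analysed.

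The cost is one table cell and a matching sentence in the analysis plan. No new data are needed: all-cause mortality is already collected, and Table 1 treats 90-day mortality as time to event, so status at day 28 can be derived. The article states that recruitment has not begun, so no analysed data are affected.

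The downside is that VFD then mixes mortality with duration of ventilation. Report it beside 28-day mortality and days of MV in survivors, so that a reader can see which part drives any difference.

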### Two-arm RCT

Eligible patients are randomised to either the model-based intervention group (MBV) or the control group (SPV). Both groups will have designated computer software to monitor their breathing [25]. The software uses real-time measurements of pressure and flow from the ventilator to objectively calculate the patient-specific and breath-specific respiratory system elastance for every breath [25].

Participants on MBV will undergo recruitment manoeuvres (RM), an initial maximum recruitment manoeuvre (RM_Max_) or subsequent PEEP adjustment and monitoring procedure (PUMP) mini recruitment manoeuvres. The respiratory elastance at each PEEP step during these protocolised RMs is calculated and recorded. The software will recommend a patient-specific minimal-elastance PEEP to the clinicians in setting ventilator PEEP. Patients on SPV will have PEEP selected using current clinical practice without the aid of the software, but all breaths will be analysed and elastance recorded; clinical staff will be blinded to these data.

#### Adherence to the intervention

Patients recruited into this study will be under constant supervision in the ICU. However, their outcomes will be measured based on the intention-to-treat principle, taking into account protocol variations, which naturally occur. These variations will be reported to the primary investigator at the earliest opportunity and followed up. There will be detailed training on the use of CURE equipment and on the protocol, to allow adherence to trial.

#### Protocol amendments

This trial is based on the intention-to-treat principle. Thus, protocol amendments may be required to ensure patient safety and outcomes, and the primary investigators will instigate protocol amendments if necessary. The amendments will be reviewed by the data monitoring committee (DMC) to warrant patient safety and outcomes. The DMC may also refer protocol amendments based on outcomes of the interim analysis reports. Finally, if participant enrolment is slow, the protocol may be amended to allow faster recruitment.

#### Concomitant care and intervention

The trial involves critically ill participants who are mechanically ventilated. Thus, it is likely and acceptable for participants to be receiving medication related to any other concomitant comorbid conditions while participating in the CURE RCT.

Participants in this study will not be concomitant to another study that would affect the results of this study. Participants will not be co-enrolled in another study that uses different oxygenation settings, recruitment manoeuvre procedures or anything that may affect the outcomes of this study.

### Eligibility criteria

The following are the CURE RCT inclusion, exclusion and P/F ratio criteria.

#### Inclusion criteria

The inclusion criteria are:
P/F ratio ≤ 200
i.on any level of PEEP or FiO_2,_ orii.P/F ratio ≤ 200 on FiO_2_ = 50% and PEEP = 5 (see “P/F ratio criteria”)

#### Exclusion criteria

The exclusion criteria are:
P/F ratio > 300 on any level of PEEP or FiO_2_P/F ratio > 200 on FiO_2_ = 50% and PEEP = 5Ventilated > 48 h (including time spent in another hospital)Not expected to be ventilated for another 48 hAge < 16 yearsAny medical condition associated with a clinical suspicion of raised intracranial pressure and/or measured intracranial pressure ≥ 20 mmHgHigh spinal cord injury with loss of motor function and/or significant weakness due to neurological diseaseBarotrauma (pneumothorax, pneumomediastinum, subcutaneous emphysema or any intercostal catheter for the treatment of air leak)Asthma as the primary presenting condition or history of significant chronic obstructive pulmonary diseaseMoribund and/or not expected to survive for > 72 hAgreed limitations of care due to co-morbidities, or not expected to survive 90 daysLack of clinical equipoise as determined by ICU medical staff managing the patient (for example, if the patient has unremarkable findings on chest x-ray, with the possibility of thrombotic or fat pulmonary emboli)Previous enrolment in the CURE RCT

#### P/F ratio criteria

The P/F ratio criteria are:
If the P/F ratio is ≤ 200, the patient is eligible for enrolmentIf 200 < P/F ratio ≤ 300, set FiO_2_ = 50% and PEEP = 5 cmH_2_O and repeat the analysis of arterial blood gases (ABG) within 10 min of the change to measure the new P/F ratio
If the new P/F ratio is ≤ 200, the patient is eligible for enrolmentIf the new P/F ratio is > 200, the patient is not eligible for enrolment and, if appropriate, will be re-screened at a later time

This trial will recruit patients who have a P/F ratio ≤ 200, a criterion in the definition of severe to moderate ARDS as defined by the ARDS Definition Task Force in the Berlin definition [26]. They will be eligible if their P/F ratio is ≤ 200 on any level of PEEP and FiO_2_. Those patients with a 200 < P/F ratio ≤ 300 will be placed on PEEP = 5 cmH_2_O, and FiO_2_ = 50%. If a subsequent P/F ratio is ≤ 200 they will also become eligible (see Additional file 1). The P/F ratio measured at FiO2 of 50% and PEEP of 5cmH_2_O is based on Villar et al. 2013 [27].

### Consent, compliance and withdrawal

#### Consent procedure

First, it is important to note that standard ventilation practice may include recruitment manoeuvres to increase lung recruitment and oxygenation. However, these clinical practices are widely variable and often not standardised. The recruitment techniques used to improve oxygenation and mechanics of ventilation in the intervention and control arms of this study are within the scope of standard ICU clinical practice. The protocols used will standardise these existing interventions to recruit lung volume and titrate PEEP.

Study participants will be unable to consent to participation in this study prior to enrolment as they will be sedated and mechanically ventilated. It is also equally important to randomise participants to either arm of the RCT at the commencement of MV to ensure a fair comparison. Patients who have been ventilated ≤ 48 h are eligible for the CURE RCT. Given this time frame, the CURE RCT will recruit patients once family consent is obtained. However, if the treating clinician firmly believes a recruitment manoeuvre is in the best interests of the patient, and no family is available for consent, the participant will be enrolled and randomised and the appropriate protocolised recruitment manoeuvre will follow. In this case, delayed consent is obtained as early as possible. Once the participant recovers from their condition and is discharged from the ICU, we will seek their informed consent.

In cases where the family cannot attend the hospital to sign a statement of assent, their opinion will be obtained by telephone in the first instance. Information about the study will either be made available by emailing them the information sheet and contacting them later by telephone, or the information sheet will be read to them over the telephone. The telephone conversation(s) and their opinions will be documented in the patient’s medical record. As soon as the family is able to attend the hospital, they will be asked to sign the statement. If the family are not able to sign a statement during the patient’s time in the ICU, they have the option of printing out the statement, signing it, and mailing, emailing or faxing it back. The sample study information and consent forms can be seen in Additional file 2.

#### Withdrawal of consent

If the participant’s family, relative or friend does not agree to their continued participation, they will be withdrawn from the study and we will seek agreement from them to use information related to mechanical ventilation that was collected up until that point.

If a participant chooses to withdraw from the trial, we also will seek agreement to use information related to mechanical ventilation that was collected up until that point. If they do not agree, then all study information obtained will be destroyed.

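### The withdrawal rule asks to keep only ventilation data, so mortality, length of stay and SAE data are not secured for withdrawn patients even when they agree, and a participant's refusal destroys everything

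*Protocol article*

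**What the plan says.** The protocol article has two withdrawal routes, both under Withdrawal of consent.

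- **Family, relative or friend.** If this person "does not agree to their continued participation, they will be withdrawn from the study", agreement is sought for ventilation information gathered so far. Nothing is said about what happens if that agreement is refused.
- **Participant.** The request has the same scope: "we also will seek agreement to use information related to mechanical ventilation that was collected up until that point". Here the consequence of refusal is stated: "If they do not agree, then all study information obtained will be destroyed". No exception is made for allocation, vital status or safety data.

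The Consent procedure section sets the timing. Family consent normally comes before enrolment. If no family is available and the clinician judges a recruitment manoeuvre to be in the patient's interest, the patient may be enrolled first: "In this case, delayed consent is obtained as early as possible". The patient's own decision comes late: "Once the participant recovers from their condition and is discharged from the ICU, we will seek their informed consent".

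These rules meet four other parts of the protocol:

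- Adherence to the intervention says that "their outcomes will be measured based on the intention-to-treat principle".
- Study design and setting lists ICU and hospital stay and hospital and 90-day mortality as secondary outcomes, and Other patient information lists mortality among the data to be collected.
- Stopping rule monitors the mortality difference between arms, with "assumed control group mortality of 0.2".
- Patient enrolment and data management counts SAE reports among the study data.

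**The concern.** The request is narrower than the list of outcomes. A withdrawer who has no objection to data use is still asked only about ventilation data. Following the text as written, the trial would have no permission to use that patient's length of stay, vital status or SAE record, although nobody refused it. That loss is avoidable and sits badly with an intention-to-treat commitment. The protocol can separate leaving the intervention from leaving follow-up: the RM checklist keeps observing and following up patients withdrawn for new barotrauma.

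The destruction clause adds a selection problem. A patient who dies in the ICU never reaches the point of being asked, so whether a record can be destroyed by this route depends on an outcome after randomisation. The trial is unblinded, and the MBV arm calls for PUMPs twice daily under deep sedation with a muscle relaxant, so refusal could differ by arm. At stake are the mortality comparisons and the mortality-based safety rule. After outright refusal, the ventilation and oxygenation outcomes are lost as well.

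**Working it through.** **1. Which data survive each case, read from the text**

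| Case | Ventilation data to date | Stay, hospital and 90-day mortality, SAE data |
|---|---|---|
| Participant agrees | kept | not requested |
| Participant refuses | destroyed | destroyed |
| Family agrees | kept | not requested |
| Family refuses | not stated | not stated |

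The second column is not secured in any row.

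**2. The plan's own mortality boundaries**

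Inputs from Stopping rule: looks at n = 50, 75, 100, 125 and 160 per arm, control mortality 0.2, linear spending, cumulative alpha 0.025. With one-sided spending of 0.025 × n/160, the critical values are 2.418, 2.479, 2.426, 2.372 and 2.268. The difference needed to stop is z × √(2 × 0.2 × 0.8 / n). At n = 160 this is 2.268 × √0.002 = 0.101. The five results are 0.193, 0.162, 0.137, 0.120 and 0.101, which match the stated 0.20, 0.16, 0.14, 0.12 and 0.10 to rounding. The boundaries are a sound yardstick.

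**3. Effect of losing survivors in one arm**

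The documents give no withdrawal or refusal rate. The shares below are assumptions. At 160 per arm, 0.2 × 160 = 32 deaths and 128 survivors.

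| Survivors lost (assumed) | Observed mortality | Shift if the other arm loses none |
|---|---|---|
| 6 (about 5%) | 32/154 = 20.8% | 0.8 points |
| 13 (about 10%) | 32/147 = 21.8% | 1.8 points |
| 26 (about 20%) | 32/134 = 23.9% | 3.9 points |

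With exact shares w, observed mortality is m / (m + (1 − m)(1 − w)). For m = 0.2 this gives 20.8%, 21.7% and 23.8%; the small differences come from rounding to whole patients.

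For a true zero difference to average 10 points at the last look, observed mortality must be 0.30. Solving 0.2 / (0.2 + 0.8(1 − w)) = 0.30 gives 1 − w = (0.2/0.3 − 0.2)/0.8 = 0.583, so w is about 42%.

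**4. Equal loss in both arms**

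With equal mortality and equal loss, the expected difference stays zero. A true 0.30 against 0.20 becomes a difference of 0.1025 at 5% loss and 0.105 at 10%.

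**5. Effect on the safety rule**

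Simulated chance of crossing any boundary with true mortality 0.2 in both arms, stopping when the observed difference is at or above the stated value (400,000 trials per scenario):

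| Survivors lost | Chance of crossing |
|---|---|
| none | 3.0% |
| MBV 5% / 10% / 20%, SPV none | 4.0% / 6.3% / 14.4% |
| SPV 5% / 10%, MBV none | 1.8% / 1.4% |
| both 5% / both 10% | 3.0% / 3.7% |

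The no-loss figure exceeds 2.5% because counts are discrete and the boundaries are rounded. Loss among SPV survivors makes the rule less likely to fire.

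**6. Direction once family withdrawal is included**

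A family can withdraw a patient who is still in the ICU and later dies. If 6 lost patients were all deaths, the same arm would show 26/154 = 16.9%, against 20.8% if all 6 were survivors. The sign depends on the mix of routes, which the documents do not give.

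**The case against.** The case on the other side is substantial.

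- **Survivor bias overall.** A reader might infer that the lost records are all survivors and that mortality is therefore overstated. The documents do not support that. Family withdrawal can lose deaths, and a patient who withdraws after ICU discharge may still die before day 90. This stands, and it makes the figures in step 3 an upper case.
- **Erased safety reports.** A reader might infer that SAE reports vanish. The DMC section says a copy of every report is forwarded as soon as it is available, and nothing says those copies are recalled. This stands for SAE reports. It does not rescue mortality, because the adverse-event section says deaths are not normally reported separately as SAEs.
- **Lost allocation.** A reader might infer that the allocation and the patient's place in the denominator also go. The text speaks of study information and does not mention the allocation list, so this is not established.
- **Intention to treat.** Analysis by allocated arm does not override a person's refusal of data use, and that statement stands in a section about adherence. This answers the refusal case. It does not answer the case of a cooperative withdrawer who is never asked.
- **Where permissions sit.** This is a condensed article, and the consent forms are in an additional file that is not shown. They may be wider. The article nevertheless states the scope of the request positively, so the point does not rest on an omission.
- **Size.** Family consent normally precedes enrolment, and nothing suggests that refusals would be frequent or differ by arm. With agreement, ventilation data to date remain usable. This stands.

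**Conclusion.** The point holds as a defect in the scope of the request. As written, withdrawal leaves length of stay, hospital and 90-day mortality and SAE data unsecured even when the withdrawer agrees to data use, and the consequence of family refusal is undefined. The explicit destruction route reaches only ICU survivors and tends to raise observed mortality in the arm affected, but the net direction across both routes is open.

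The size is modest. It rests on assumed loss rates, on all loss falling in one arm, and on all lost patients being final survivors. On those terms the spurious difference is 0.8 to 1.8 points at 5% to 10% loss and 3.9 points at 20%, against a final boundary of 10. A reader might infer that the clause could by itself drive the trial to a false safety stop. That would need about 42% of one arm's survivors to be lost for the average difference to reach the boundary, and nothing in the documents suggests loss on that scale. The case for change is that the loss is avoidable and cheap to prevent.

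**What to change.** Reword Withdrawal of consent as follows.

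1. Separate ending study procedures from ending data use, and treat withdrawal as the first unless the person says otherwise.
2. Ask participant and family alike, item by item, for agreement to (a) keep all data collected to date, not only ventilation data, and (b) obtain ventilation days, length of stay and 90-day vital status from hospital records.
3. State what happens to the data if the family refuses.
4. State whether SAE copies already held by the DMC are retained.
5. Report withdrawals and data refusals by arm.

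After full refusal, a minimal record of arm, dates and SAE reports should be kept only as far as ethics approval allows; the documents do not settle that question.

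The cost is an ethics amendment and revised consent forms, with no new assessments. Some patients may still refuse. The change belongs before the first enrolment, since destroyed records cannot be recovered, and Trial status says recruitment had not begun.
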